### 3.1. Inclusion Process

When a child enters this study, we will not intervene in any prescribed therapy and medication. We plan to include a thousand children (with a possible dropout rate of 5%), which will be possible due to a collaboration with a selected number of schools in Region Hovedstaden and Sjaelland. All participants will be recruited through the director of the participating school. One local co-investigator (not associated with this study) will be appointed from each school. The inclusion process will continue until a total of a thousand subjects are included in this study. The project coordinator and the co-investigator at each school will send out a specific link to relevant information for the possible candidates and obtain a signed informed consent. This link will be mediated via the Danish parental-school communication channel, the Aula portal. Access to Aula will be through parents or guardians who must log in with the Danish national identification service NemID. The data, which are mediated, are stored in Europe. Aula is hosted by Amazon Web Services (AWS). AWS is an American-owned company that provides cloud solutions and has data centers in Ireland, Germany, and France, among others. However, part of the Aula agreement is that data must be located in an EU/EEA country. Data in the Aula system are encrypted. Data are encrypted throughout the process. The keys to the encryption are securely stored in Denmark, and Aula complies with the GDPR rules and rules regarding IT auditing. This is mediated through a previously approved procedure in Region H for the Redcap database and a similar procedure has been approved in a project in ‘De Videnskabsetiske Komitéer for Region Midtjylland’. As mentioned, all participants will then be recruited using a method that is approved by the local information security service CIMT, region H, Copenhagen Denmark*, where we will obtain consent for a research project using the REDCap system by asking the subjects and caregivers for consent to participate in a project using the following procedure: The subject and caregiver log on to Aula with NemID.A link to RedCap is sent via Aula to the subject and caregiver (who has now been verified via the NemID login).The subject and caregiver enter RedCap to be able to assess written patient information and preliminary oral information via video, with the possibility to orally inquire about additional information on the project (see below).After this, they will be able to confirm his/her consent by signing into the digital system.

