### 6.3. Statistical Analysis and Randomization 

Three clusters of equally divided children from the 1st grade, 5th grade, and 9th grade will be evaluated. This was chosen to embrace the spectrum of chronological (with different developmental stages) ages in Danish primary schools. The total planned number of included children is a thousand children. The sample size was chosen based on a balance between the desired statistical robustness and the practical constraints of this study. These constraints include available resources, such as funding, staffing, and logistics. This sample size is in line with or larger than similar large-scale, observational studies in pediatric populations [36,37,38], where specific power calculations can be more complex due to the multitude of variables and outcomes being explored. We acknowledge this as a limitation but also believe that the chosen sample size is sufficient to provide meaningful and robust data for the objectives of our study. The schools will be chosen randomly with the measure of crow fly distance and the number of children in the schools (>1000). A school’s socioeconomic status will be registered based on the ‘Socioøkonomisk reference for grundskolekarakterer 2018/2019′ [36]. The normality of the data will be assessed graphically using quantile–quantile and density plots. 

Based on their distribution, variables will be described using either means and standard deviations (for normally distributed data) or medians and interquartile ranges (for non-normally distributed data). Appropriate hypothesis tests will be conducted based on the distribution of the data. These include Student’s t-test and Wilcoxon’s rank-sum test for continuous data. For categorical data, chi-square tests and Fisher’s exact test will be used as appropriate. *p*-values of ≤ 0.05 will be considered statistically significant. Simple bivariate analyses will be conducted to establish initial associations between potential predictor variables and relevant outcome variables. To investigate the associations between pain and lower extremity kinematic and alignment variables, we will use multilevel multivariable logistic regression models, stratified by grade (1st, 5th, and 9th). Examiner ID will be included as a random factor in the models. The statistical analysis will be performed using the newest available version of R [39].

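### Section 6.3 names the pooled-variance t-test and checks only normality, so in bivariate comparisons of unequal groups the 5% level is not guaranteed; naming Welch's test is a cheap improvement

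*Protocol article*

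**What the plan says.** Section 6.3 of the protocol article sets out a short sequence. Normality is judged from quantile–quantile and density plots. Then "Appropriate hypothesis tests will be conducted based on the distribution of the data", and "These include Student’s t-test and Wilcoxon’s rank-sum test for continuous data". The significance threshold of p ≤ 0.05 is stated once, for all tests.

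The role of the two-sample tests follows: "Simple bivariate analyses will be conducted to establish initial associations between potential predictor variables and relevant outcome variables". No grouping variable is named for them. For pain in relation to kinematic and alignment variables, a separate analysis is named: "we will use multilevel multivariable logistic regression models, stratified by grade (1st, 5th, and 9th"), with examiner as a random factor.

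On numbers, the article says "The total planned number of included children is a thousand children" and "Three clusters of equally divided children from the 1st grade, 5th grade, and 9th grade will be evaluated". It gives no pain prevalence, no prevalence of any pathology and no SD. Estimating the prevalence of pain and of foot pathologies is itself one of the three purposes in the Introduction.

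**The concern.** Student's test estimates one common variance from both groups. The larger group dominates that estimate. If the smaller group is more variable than the larger one, the standard error of the difference is too small and the test rejects too often. If it is less variable, the test rejects too rarely. A normality plot does not show which case applies, because two normal samples can have quite different spreads.

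The setting makes unequal groups plausible. Section 5.2 records many continuous measurements (ranges of motion, torsion, navicular height) alongside yes/no pathologies. Section 5.3 lists pain status as an endpoint and plans to relate the Oxford foot score to foot pathologies. In unselected schoolchildren, a split by pain or by one pathology need not be anywhere near half and half. At stake is what the label 'significant' means for a bivariate result when the actual error rate depends on an assumption that the plan does not look at.

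**Working it through.** **No figure of the plan to reproduce.** The sample size rests on resources and on comparison with similar studies. There is no power calculation, effect size or SD. The only stated figure to test against is the 5% level.

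**Inputs.** From section 6.3: level 0.05 (taken as two-sided), 1000 children in three equal grades, so 1000/3 ≈ 333 per grade. Assumed, because the article does not give them: share p of children in the smaller group, and ratio r of its SD to that of the larger group.

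**Formula.** Set the larger group's SD to 1, the smaller group's SD to r, and q = 1 − p. In large samples:

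- variance that Student's test assumes for the mean difference: (p·r² + q)/(N·p·q)
- true variance: (q·r² + p)/(N·p·q)
- ratio R = (p·r² + q)/(q·r² + p)
- true size = 2·[1 − Φ(1.960·√R)]

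N cancels, so the size depends on the split and the SD ratio and hardly on whether one grade or the whole sample is used.

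**Two cases where nothing goes wrong.** If r = 1, then R = (p + q)/(q + p) = 1. If p = q = 0.5, then R = 1 for any r. In both, the size is 5%.

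**Worked examples.**

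- p = 0.20, r = 1.5: R = (0.45 + 0.80)/(1.80 + 0.20) = 0.625; 1.960 × 0.791 = 1.550; size 12.1%.
- p = 0.10, r = 1.5: R = (0.225 + 0.90)/(2.025 + 0.10) = 0.529; 1.960 × 0.728 = 1.426; size 15.4%.
- p = 0.10, r = 0.67: R = (0.045 + 0.90)/(0.404 + 0.10) = 1.875; 1.960 × 1.369 = 2.684; size 0.7%.

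**True size of Student's test at nominal 5%.**

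| Smaller group | r = 0.67 | r = 0.8 | r = 1 | r = 1.25 | r = 1.5 |
|---|---|---|---|---|---|
| 10% | 0.7% | 1.9% | 5% | 10.1% | 15.4% |
| 20% | 1.3% | 2.5% | 5% | 8.6% | 12.1% |
| 30% | 2.2% | 3.2% | 5% | 7.3% | 9.3% |
| 50% | 5% | 5% | 5% | 5% | 5% |

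Simulation with normal data, 100,000 data sets per setting, at N = 333 and N = 1000, reproduces these values to within about 0.2 points. Welch's test gives 4.9% to 5.2% in every setting.

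**Cost of Welch's test when the variances are equal.** The difference was set for 80% power by the normal approximation, d = (1.960 + 0.842)·√(1/n₁ + 1/n₂); for 67 v 266 this is 0.383 SD. Simulated power:

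| Groups | Student | Welch | Loss (points) |
|---|---|---|---|
| 67 v 266 | 79.8% | 79.3% | 0.5 |
| 33 v 300 | 79.9% | 78.1% | 1.7 |
| 17 v 316 | 79.8% | 75.3% | 4.5 |

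Losses are computed before rounding. With all 1000 children the loss is smaller: 0.2 points at 200 v 800 and 0.5 at 100 v 900.

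**The case against.** The strongest reply is that section 6.3 does not commit to what is criticised. The list of tests is open, the choice is to be appropriate to the data, the unequal-variance form is not excluded, and no grouping variable is named. The article condenses a fuller plan, which may settle the variant. For pain with kinematic and alignment variables the named analysis is the multilevel logistic model, and the bivariate tests are only a first look. Comparisons between two of the equal-sized grades would be balanced, where Student's test is safe.

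Most of this stands, and it limits the point. It does not remove it. The article names Student's test, which is the pooled form, and the one assumption check that it describes does not cover equality of spread. That is a stated choice for which a better one exists, not a detail left out.

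A reader might infer more: that the 5% level is definitely broken in the pain comparisons because the pain group is small and more variable. The article does not support that. It gives neither a pain prevalence nor an SD, and does not tie the t-test to pain against no pain. Even the direction of any error is unknown. Nor is the switch to Welch's test free, as the power figures show.

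**Conclusion.** The point holds as a low-severity improvement. Where a bivariate comparison is between unequal groups whose SDs also differ, the error rate of the named test is not guaranteed to be 5%. With 10–20% of children in the smaller group and SD ratios from 0.67 to 1.5, it lies between about 1% and 15%. These splits and ratios are assumptions; with equal SDs or balanced groups the test is at its nominal level.

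The consequence stays within the bivariate results. The multilevel logistic models for pain do not use this test and are unaffected. Foot dimensions, plantar pressure, shoe fit and the foot-health score are not expressly listed for those models, so the choice of bivariate test may carry more weight there.

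**What to change.** In section 6.3, replace 'Student's t-test' by 'Welch's unequal-variance t-test'. No separate test of equal variances is then needed.

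In the plan this is a change of a few words, and in the R code it is one option. The price is the power loss shown above: at the size of one grade, about 0.5 to 2 points when the smaller group holds 10–20% of the children, rising to about 4.5 points when it has fewer than 20. No data collection, sample size or regression model changes.

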
## 1. Introduction

The well-being of children, and the health of children’s feet, is a priority for a range of professionals, such as school nurses, pediatricians, general practitioners, pediatric orthopedics, and podiatrists [1,2]. Social inequality impacts general health in an environment of growing social differences in an increasingly fragmented healthcare system and might raise barriers to accessing qualified health care, thus indicating a need for either rehabilitation and preventive actions or information on healthcare issues concerning children’s diseases of the lower extremities and feet, and a study evaluating the need of healthcare services indicates that this might not reach medical consultation [3,4,5,6,7]. Healthy feet are a prerequisite for many physical activities, and painful feet may inhibit children in physical exercise and give a decreased quality of life [8,9,10]. Children can have painful feet for a plethora of reasons, and structural differences may have an impact on pain and level of activity. Parents and grandparents are concerned that children with in-toeing, flat feet, and curly toes may develop pain or disability, and healthcare workers must be able to differentiate between what are merely physiological variations and what may lead to detrimental conditions as a child grows older. Previous studies indicate that children are born with “flat feet’’ [11,12,13,14] and that the longitudinal medial arch is not fully developed until a child is 6–7 years old [15,16]. Therefore, several studies have failed to show that insoles and special shoes in preschool children change the natural history of flat feet [17]. However, studies examining anthropometric parameters of the lower extremities and feet have not been performed in older children, and little is known about how this affects an older child in relation to pain and how this may affect their participation in sports and other physical activities. Children with flat feet may have a reduced quality of life, thus motivating interventions. A recent study indicates that insoles in older children may change the osseous construction of the foot and thus, may prevent painful flat feet in adults [18]. Therefore, insoles may have the potential to prevent painful flat feet in adults and potentially prevent surgery for this condition in adults [19]. For these motivating reasons, the pediatric orthopedics section of the Rigshospitalet and Hvidovre Hospital, the University of Southern Denmark, and the Association of Danish Podiatrists have started a project for the evaluation and screening of children’s feet and lower extremities in Danish primary schools. Wearing shoes can be underestimated concerning the health of children’s feet, but a too-tight-fitted shoe is known to predispose to hallux valgus and lead to foot pain in children [20,21,22]. Studies in the European setting indicate that children in these countries often wear shoes that are too small [23,24]. The effect of shoe fit also impacts the development of pathological diseases such as apophysitis of the calcanei, and simple ingrown toenails and may give rise to deformities, ingrown toenails, or non-specific foot pain [20,22,25]. In this study, we plan to evaluate this using the commercial technology of 3D surface scanning and evaluate the appropriateness of shoe fitting via the measurement of shoe size. The perspective of this study is that we, in the future, will be able to provide recommendations for preventive actions for children for improvement in the care of the health of children’s lower extremities and feet, thus demonstrating the potential for long-term health and societal financial benefits, such as referral to other health services, guidance on sensible footwear, foot care, and hygiene. The purpose of this project is to identify anthropometric parameters that might be preconditions for pain, evaluate for foot diseases and whether they are associated with pain intensity and location, three-dimensional foot dimensions and foot pressure mapping, shoe dimensions, intensity and type of sports activity, and status of quality of life and foot health according to patient-related outcome measures (PROMs). The aim is that we will be able to identify parameters pre-dispositioning for pain, thus providing recommendations for sports activities in relation to the anthropometric conditions of a child as a potential preventive measure for pain. Our purpose with this study is threefold:To make reference material of the demography of the foot, the rotational status, and the range of motion in joints in the lower extremities of children in Denmark to evaluate if these anthropometric parameters in children influence pain status.Examining the prevalence of pain in children as well as exploring the prevalence of pathologies in children’s feet to evaluate if these conditions in children influence pain status.Evaluating the appropriateness of shoe fitting using commercial 3D technology and foot pressure mapping to evaluate if shoe fitting in children influences foot pain status.

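### Grade stratification is promised only for the kinematic and alignment models; shoe fit, plantar pressure, foot size and other pathologies are left with bivariate tests that do not condition on grade

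*Protocol article*

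**What the plan says.** Section 6.3 of the protocol article lists Student's t, Wilcoxon rank-sum, chi-square and Fisher's exact tests and treats p "values of ≤ 0.05 will be considered statistically significant". It continues: "Simple bivariate analyses will be conducted to establish initial associations between potential predictor variables and relevant outcome variables". The next sentence turns to pain and the kinematics and alignment of the lower extremity, and there "we will use multilevel multivariable logistic regression models, stratified by grade (1st, 5th, and 9th". Grade appears in no other analysis sentence.

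The same section fixes the sample: "The total planned number of included children is a thousand children", and "Three clusters of equally divided children from the 1st grade, 5th grade, and 9th grade will be evaluated". The reason for three grades is developmental: "This was chosen to embrace the spectrum of chronological (with different developmental stages) ages in Danish primary schools".

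The third objective, in section 1, is "Evaluating the appropriateness of shoe fitting using commercial 3D technology and foot pressure mapping to evaluate if shoe fitting in children influences foot pain status". The second objective asks the same of foot pathologies. Section 7 intends to build recommendations on foot dimensions and pressure mapping, among other findings.

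**The concern.** Shoe fit and plantar pressure are neither kinematic nor alignment variables. The same holds for foot length and girths, and for conditions such as warts or ingrown toenails. For these the article names no analysis after the bivariate one, so calling that step initial does not protect them.

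A two-variable test across three developmental stages compares children with pain and children without pain who may differ in grade mix. Foot length and girths grow between first and ninth grade. If pain also differs by grade, the test can reject even though, among children of the same grade, the variable has nothing to do with pain. In the other direction, if misfit falls while pain rises with grade, a true shoe-fit association can be diluted. The stated question is about the individual child's foot or shoe, and the answers are meant to feed preventive recommendations.

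**Working it through.** **Inputs from the article.** N = 1000 in three equal grade groups, about 333 each (1000/3); threshold 0.05, taken as two-sided because sidedness is not stated. The article gives no power, effect size or rejection rate, so there is no figure to reproduce.

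**Assumed inputs.** Pain rates by grade, the shift of the predictor per grade step (in within-grade SDs) and misfit rates by grade. None is in the article.

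**1. Mechanism by hand.** Take pain 15/20/25%, a predictor rising 1 SD per grade step, and no link within grade. Code the grades 0, 1, 2.
- Mean grade code with pain: (0×0.15 + 1×0.20 + 2×0.25)/0.60 = 0.70/0.60 = 1.167.
- Mean grade code without pain: (0×0.85 + 1×0.80 + 2×0.75)/2.40 = 2.30/2.40 = 0.958.
- Spurious mean difference: 0.208.
- SD across grades: √(1 + 2/3) = 1.291.
- Group sizes from 3×333 = 999: about 200 and 799. SE = 1.291×√(1/199.8 + 1/799.2) = 0.102.
- z = 0.208/0.102 = 2.04, so the rejection rate is about Φ(2.04 − 1.96) = 0.53.

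**2. Simulation.** False-rejection rate of a t-test across grades with no within-grade link, 4000 runs per cell:

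| Pain by grade | shift 0.5 SD | 1 SD | 2 SD |
|---|---|---|---|
| 20/20/20% | 0.05 | 0.05 | 0.04 |
| 18/20/22% | 0.07 | 0.12 | 0.20 |
| 15/20/25% | 0.23 | 0.53 | 0.79 |
| 10/20/30% | 0.69 | 0.99 | 1.00 |
| 15/25/15% | 0.05 | 0.05 | 0.03 |

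The 0.53 agrees with step 1. With no shift in the predictor, the rate was 0.04 to 0.05 for every flat or rising pain pattern. A grade-stratified combined test stayed at 0.04 to 0.05 in all the flat and rising scenarios.

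**3. Shoe misfit as a yes/no variable, no within-grade link.** Assume misfit 70/50/30% and pain 15/25/35%.
- Misfit among children with pain: (0.15×0.7 + 0.25×0.5 + 0.35×0.3)/0.75 = 0.447.
- Misfit among children without pain: (0.85×0.7 + 0.75×0.5 + 0.65×0.3)/2.25 = 0.518.
- Difference −0.071; SE = √(0.25×(1/250 + 1/750)) = 0.0365; |z| = 1.95; rejection about 0.49.

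Simulation gives 49% here, 17% with pain 20/25/30%, and 8 to 9% with 22/25/28%. Mantel-Haenszel stays near 5%.

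**4. Masking.** Keep misfit at 70/50/30%, set pain without misfit at 15/25/35%, and let the true within-grade odds ratio be 1.6.
- Pain with misfit becomes 22.0/34.8/46.3%.
- Across grades, pain with misfit: (0.7×0.220 + 0.5×0.348 + 0.3×0.463)/1.5 = 0.311.
- Across grades, pain without misfit: (0.3×0.15 + 0.5×0.25 + 0.7×0.35)/1.5 = 0.277.
- Crude odds ratio: (0.311/0.689)/(0.277/0.723) = 1.18, against the true 1.6.

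Simulated power is 21% for the crude chi-square against 87% for Mantel-Haenszel. With pain without misfit at 20/25/30%, it is 64% against 89%.

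**The case against.** The article never says that the grades are pooled. It is a condensed account, and whether initial bivariate tests run by grade could be settled in a fuller plan. It calls the step initial, and its named pain models are stratified by grade. The class of kinematic and alignment variables is not enumerated: range of motion, hindfoot valgus and hallux valgus may well belong to it, and arch height could too. Lengthwise shoe fit (section 5.4.2) is inside shoe length minus the child's own foot length, so it is already relative to foot size. Reporting crude associations first is ordinary practice, and a crude test is a valid test of marginal association.

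Much of this stands. It rules out the stronger reading that a reader might infer, namely that the plan pools the grades, that pain rises with grade, and that the tests will therefore reject. The article states neither of the first two. The third fails on the figures, because the rate stays near 5% when pain is flat, or under the symmetric non-monotone pattern tried. The near-100% figures apply to continuous variables with steep trends, not to yes/no misfit.

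What the objection does not remove is the limited scope. The article did not leave grade stratification to another document: it stated it, and gave it a scope that does not clearly include shoe fit, pressure, foot size or non-alignment pathologies. Measuring fit against the child's own foot does not stop misfit from varying by grade.

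**Conclusion.** The point holds in a limited, conditional form. As written, the grade-stratified pain models do not reach shoe fit, plantar pressure, foot size dimensions or non-alignment pathologies, and the only association analysis named for them does not condition on grade. Two tests of two variables each, with stratification mentioned only in the following sentence for another question, read most naturally as run across grades; that remains an inference.

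The consequence depends on trends that the article does not give. Confounding needs both the variable and pain to differ by grade. Under the assumed patterns, false rejection ranges from about 5% to nearly 100% for continuous variables and from 8 to 9% up to 49% for shoe misfit at 70/50/30% with rising pain. Masking needs misfit and pain to trend in opposite directions. This is a free improvement to the plan; it does not show that any result will be wrong.

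**What to change.** In section 6.3:

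- Extend the grade-stratified (or grade-adjusted) pain models to shoe fit, 3D foot dimensions, plantar pressure and foot pathologies, so that the second and third objectives have a named analysis that accounts for grade.
- Run the bivariate pain associations within grade or conditional on grade: for example Cochran-Mantel-Haenszel for categorical variables, and van Elteren or a linear model with grade terms for continuous ones.
- Show grade-specific estimates beside one combined estimate. Relying on three separate tests at 0.05 would give at least one false rejection in 1 − 0.95³ = 14% of cases.
- Label any crude result across grades as descriptive.

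The cost is a few sentences and a few lines of R. Grade is known for every child, so no new data are needed. Some crude associations may disappear. Section 6.1 says preliminary analyses are under way, so the wording should be settled now.

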## Abstract

Background: The health of children’s lower extremities and feet is a focus area for caregivers and healthcare professionals such as doctors, school nurses, and podiatrists. Our study aims to investigate the general health status of Danish children’s lower extremities and feet to identify anthropometric parameters that might be preconditions for pain and evaluate for foot diseases and whether they are associated with pain intensity and location, three-dimensional foot dimensions and foot pressure mapping, shoe dimensions, types and intensity of sports activity, quality of life, and foot health. The aim is that we will be able to identify parameters pre-dispositioning for pain, thus providing recommendations for sports activities in relation to the anthropometric conditions of a child as a potential preventive measure for pain. This analysis will be stratified by socioeconomic status on a group level, and this perspective will be able to provide preventative recommendations to prevent pain. Methods: This study is a cross-sectional examination of a thousand children in the first, fifth, and ninth grades in randomized selected Danish primary schools. We will perform a clinical examination of the lower extremities and feet for misalignments, deformities, and diseases as well as rotational status and range of motion. Moreover, we will evaluate their pain levels, sports activities, three-dimensional foot dimensions, plantar pressure, footwear, and patient-related outcome measures (PROMs) for foot health and quality of life. Results: We aim to provide an anthropometrical overview of the lower extremities and feet in children. The obtained basic understanding of healthy normal material in children will be analyzed for its relationships with pain level, sports activities, and socioeconomic status on a group level. This could potentially provide us with an understanding of the factors that impact lower extremity and foot diseases in children. In conclusion, examining children’s lower extremities and feet in Danish primary schools is a step toward identifying areas of improvement in self-care and shoe fitting, mapping podiatry-related needs of care in children’s feet, and providing parental recommendations for preventive actions on shoe fitting and the choice and intensity of sports activity concerning pain. Conclusions: The tenet of this study is a long-term follow-up to evaluate the long-term socioeconomic course on a group level, foot status, and sports activity, using patient-related outcome measures evaluating quality of life and other lifestyle factors such as emotional functioning, social functioning and interaction, and school functioning. Potentially, this will improve children’s quality of life and prevent future diseases.

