## 2. Method and Materials

### 2.1. Study Design

The design of this study is a cross-sectional examination or a clinical and observational study of children in the first, fifth, and ninth grades in Danish primary schools. The schools will be selected randomly by their socioeconomic profiles. Our focus will be on analyzing their clinical status, pain levels, foot dimensions and pressure, and footwear. Specifically, we plan to evaluate misalignments, malpositions, deformities, skin and foot hygiene, and the rotational status of the lower leg, as well as the range of motion in the lower extremities of the children. These data will serve as a reference for the foot demographics and provide insights into the health of children’s feet. We will enquire about foot health and quality of life using PROMs, and we will measure foot dimensions using 3D scanning techniques on the children’s feet and assess the quality of their footwear by evaluating shoe sizes with scientific measurements. This will help us determine if there is a mismatch between footwear and foot size, which could potentially lead to deteriorating foot health in children. Additionally, we plan to collect data on foot pressure mapping to determine the pressure points on the children’s feet. We will evaluate their pain status based on the anatomical pain location, type, and intensity using numerical pain rating scales. 

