#### 2.1.2. Study Organization

This study is organized under the leadership of a senior medical consultant and one senior researcher who oversees the employment and supervision of a team of researchers. The team consists of three medical students (TAP), four doctors, six podiatrists, one project coordinating nurse, and one senior researcher as a collaborator. Regularly scheduled meetings are held throughout the school year, with ad hoc meetings as necessary to ensure effective coordination and collaboration among team members. This study will be conducted in collaboration with 20 schools at different locations in Region Hovedstaden and Region Sjaelland. 

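### Schools are the sampled units and carry the socioeconomic variable, but section 6.3 names only examiner ID as a random factor and states no model for the promised socioeconomic analysis

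*Protocol article*

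**What the plan says.** **Sampling.** Section 2.1 makes the school the unit that is drawn: "The schools will be selected randomly by their socioeconomic profiles". Section 2.1.2 gives the number: "This study will be conducted in collaboration with 20 schools at different locations in Region Hovedstaden and Region Sjaelland". Section 6.3 gives the total: "The total planned number of included children is a thousand children".

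**Grades.** Section 6.3 uses the word cluster for the grades and not for the schools: "Three clusters of equally divided children from the 1st grade, 5th grade, and 9th grade will be evaluated".

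**Socioeconomic status.** The abstract commits to using it: "This analysis will be stratified by socioeconomic status on a group level". Section 6.3 measures it per school: "A school’s socioeconomic status will be registered based on the", followed by the name of a national reference for school marks. Section 6.3 then gives it no role in a model or test.

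**Models and tests.** For pain and alignment, "we will use multilevel multivariable logistic regression models, stratified by grade (1st, 5th, and 9th". The next sentence is "Examiner ID will be included as a random factor in the models". For other comparisons, section 6.3 lists the t-test, the Wilcoxon rank-sum test, chi-square and Fisher's exact test. No section mentions a school effect, school-clustered errors or a design effect.

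**The concern.** Children at one school share a catchment area, local sports provision and shoe-buying habits, so their outcomes may be correlated. Where they are, a prevalence or a school-level comparison carries less information than the number of children suggests.

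Section 6.3 recognises that observations may be correlated, since it calls the models multilevel and names a random factor. The factor it names is the measurer and not the unit through which children were sampled. Six podiatrists are listed in section 2.1.2, and section 6.1 has podiatrists doing the examinations. Six examiners cannot stand in for 20 schools.

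Two declared aims are exposed. One is the prevalence of pain and foot pathology, which is among the three numbered purposes in the introduction. The other is the socioeconomic perspective, which the abstract, the introduction and section 7 all promise. For the second, there are at most 20 independent values of the explanatory variable, however many children are examined.

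**Working it through.** **The plan's own figure.** The 1000 was set on practical grounds. Section 6.3 gives no effect size, power or ICC, so there is no calculation to reproduce.

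**Inputs.** From the article: 1000 children, 20 schools, three equal grade groups, significance at 0.05 (taken as two-sided). Assumed, because the article gives none: school ICC of 0.01, 0.02 or 0.05.

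**Cluster sizes.** Pooled: 1000/20 = 50 children per school. Within a grade: 1000/(3 × 20) = 16.7 per school, in a grade group of about 333.

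**Formulas for a prevalence or school-level covariate.** Design effect DE = 1 + (m − 1) × ICC. The true standard error is the naive one times √DE. Effective n = n/DE. For a contrast on a school-level covariate tested as if children were independent, the true two-sided error is 2 × [1 − Φ(1.96/√DE)]. Example: m = 50 and ICC = 0.02 give 1 + 49 × 0.02 = 1.98.

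| Setting | ICC | DE | SE multiplier | Effective n | True error at nominal 5% |
|---|---|---|---|---|---|
| One grade, m = 16.7, n = 333 | 0.01 | 1.16 | 1.08 | 288 | 6.8% |
| | 0.02 | 1.31 | 1.15 | 254 | 8.7% |
| | 0.05 | 1.78 | 1.34 | 187 | 14.2% |
| Pooled, m = 50, n = 1000 | 0.01 | 1.49 | 1.22 | 671 | 10.8% |
| | 0.02 | 1.98 | 1.41 | 505 | 16.4% |
| | 0.05 | 3.45 | 1.86 | 290 | 29.1% |

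Illustration for a prevalence assumed to be 20%, pooled: the naive 95% half-width is 1.96 × √(0.2 × 0.8/1000) = 2.5 points. Multiplied by √DE it becomes 3.0, 3.5 and 4.6 points.

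**Does the examiner term absorb the school effect?** This was simulated for one grade: 20 schools of 17 children, six examiners, about 25% pain, a school-level covariate with no effect, and 2000 runs per setting. Examiner was entered as fixed dummies in place of a random factor. At ICC 0.02, 0.05 and 0.10 on the latent logistic scale, rejection at nominal 5% was 6.6–8.2%, 9.8–10.6% and 16.2–17.2%. Each range covers examiners crossed with schools and one examiner per school. So adjusting for examiner leaves the problem in place.

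The latent scale is not the scale of the table. With σ² = ICC/(1 − ICC) × π²/3 and p = 0.25, the observed-scale value is roughly p(1 − p)σ²/[1 + p(1 − p)σ²], which is 0.012, 0.031 and 0.064. With m = 17 the formula then gives DE 1.20, 1.50 and 2.03 and true error of about 7%, 11% and 17%, in line with the simulation.

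**Child-level covariates.** Here DE = 1 + (m − 1) × ICC_x × ICC_y, where ICC_x is the covariate's own clustering by school. Within a grade, with ICC_x = 0.05 and ICC_y = 0.02 or 0.05, DE = 1.02 or 1.04 and the true error is 5.2% or 5.5%. The simulation gave 4.6–6.0% at latent ICC 0.02 to 0.10. Pooled, with both at 0.05, DE = 1.12 and the error is 6.4%. The same formula shows that a bivariate test is disturbed only as far as its grouping variable differs between schools.

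**The case against.** **Scope.** The sentence about examiner ID belongs to grade-stratified models of pain on child-level alignment variables. A reader might infer that every standard error and p-value from those models is too small. The documents do not support that: for alignment variables that vary little between schools, the loss is close to nil. This objection stands and limits the point.

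**No stated socioeconomic test.** Section 6.3 specifies none, so a reader cannot conclude that one will be done at child level with inflated error. A group-level stratification could mean description by subgroup or a comparison of school means. This also stands. The error rates are conditional on a child-level analysis, and the pooled ones also require grades to be combined, which the stated models do not do. What remains is that the analysis is promised and no model carries it.

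**No stated prevalence intervals.** It is tempting to say that prevalence intervals will be too narrow. Section 6.3 states no such intervals, so the point covers only any that are reported.

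**Silence is not exclusion.** The article condenses a fuller plan, and a multilevel model might contain a school level that is not mentioned. That is possible. But the article does not leave the random structure open: it names a factor, and the factor is not the sampled unit. An analyst following the text would leave school out.

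**Unknown ICC.** At an ICC of zero nothing is lost. The range is an assumption, and the design gives no reason to plan on zero.

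**Conclusion.** The concern holds with a defined scope. Section 6.3 names a random factor that is not the sampled unit, lists tests that assume independent children, and never carries the abstract's socioeconomic analysis into a model. The gap between the abstract and section 6.3 holds whatever the ICC.

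The numerical consequence requires a school ICC above zero. At 0.01 to 0.05, standard errors for a prevalence or school-level contrast should be 1.08 to 1.34 times the naive ones within a grade, and 1.22 to 1.86 times pooled. A socioeconomic contrast run at child level would reject a true null in about 7% to 14% of cases within a grade and 11% to 29% pooled. The calculation takes equal numbers of children per school and uses a normal approximation.

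The associations between pain and child-level alignment variables are not seriously threatened, provided those variables vary little between schools.

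**What to change.** In section 6.3:

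- Add a random intercept for school beside examiner ID in the logistic models. If the crossed model does not converge, use school-clustered standard errors with a small-sample correction for 20 clusters.
- State the socioeconomic analysis: the school's socioeconomic reference enters as a school-level covariate and is tested against between-school variation, with about 20 − 2 = 18 degrees of freedom. Bring the abstract's wording on stratification into line with this.
- Use school-clustered standard errors for bivariate comparisons and for any prevalence intervals that are reported.

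No new data are needed: socioeconomic status is assigned by school, so school must be identifiable for each child. The work is a few lines of R and a paragraph of text. Section 6.1 describes the analyses as preliminary, so the change can still be made before the final ones.

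There are two real costs. Intervals will be wider. Convergence may also be difficult: at an assumed 20% pain there are about 16.7 × 0.2 ≈ 3 events per school and grade. That is why the fallback should be written down in advance.
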